## Methods

### Study design and data management

The FinnTrunk study is a non-blinded, multicenter, parallel-group, randomized, controlled study, which will be conducted in four large Finnish hospitals (Helsinki University Hospital, Oulu University Hospital, Satasairaala hospital in Pori, and Turku University Hospital). The participating hospitals were selected based on the high volume of endovenous procedures in their respective vascular surgery units. Data will be collected by study investigators at each participating center and uploaded to an electronic data capture system (REDCap, Vanderbilt University, Nashville, TN, USA) hosted by and at Helsinki University Hospital. The FinnTrunk study was registered on ClinicalTrials.gov on 24 February 2021 (study identifier NCT04774939), and the first patient was entered in the study register on 6 October 2021. The first study results will be published in a peer-reviewed journal in 2024.

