### Patient enrolment and randomization

The patients who fulfill the study criteria will be given a brief information letter and offered the possibility to participate in the study. The baseline characteristics of the patients who give their written informed consent will be recorded in the study register. The patients will fill in the Aberdeen Varicose Vein Questionnaire (AVVQ) [27] (with question 1 omitted [28, 29]) and the EQ-5D-5L, while the investigator will ascertain and record the patient’s Venous Clinical Severity Score (VCSS) [21], Venous Disability Score (VDS) [30], and the clinical class of the Clinical-Etiology-Anatomy-Pathophysiology (CEAP) classification [20], in addition to recording the location and extent of the varicose tributaries.

The patients will be randomly allocated with the REDCap to one of the two study groups before the procedure. Patients in group one will be treated with EVLA of the incompetent saphenous trunk without treatment of the varicose tributaries. Patients in group two will be treated with UGFS of the varicose tributaries concomitantly with the EVLA.

If the patient wishes to decline participation in the study, they will be treated according to the usual regime of the unit.

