### Outcome measures and follow-up

The duration of the follow-up will be five years. The primary outcome measure will be the need for additional treatment of the varicose tributaries during the follow-up, as judged by the patient. The secondary outcome measures will be the cost of treatment and recurrence of varicose disease. Other outcome measures of interest will the length of the procedure time and the impact of treatment on the Aberdeen Varicose Vein Questionnaire (AVVQ) score, the Venous Clinical Severity Score (VCSS), health-related quality of life (the EuroQoL EQ-5D-5L) score, and patient-related outcome measures (PROMs). Data pertaining to PROMs will be collected at 1 year with two questions: “Was the treatment you were given of good quality?” and “Did the treatment you were given meet your expectations?”

In addition, the following data will be collected at the 3-month follow-up visit: pain score based on numeric rating scale (NRS) during the procedure and at three time points post-procedure, the use of analgesics, and the possible procedure-related complications. Patients will also be asked about the duration of sick leave and for their estimate of the appropriate recovery time.

The study leg will be assessed using DUS at each follow-up visit. The protocol for the examination will be identical with the diagnostic DUS described previously under Study setting and patient screening, i.e., the diameter of GSV and SSV will be measured and both veins will be assessed for patency and reflux regardless of whether the vein has been treated or not; the AASV will be systematically assessed only when it has been the target for ablation. Apart from that, it will be assessed as needed, i.e., if there are varicose tributaries that could be connected to the AASV. The treated saphenous trunk will be assessed according to the recommendations and definitions of De Maeseneer et al. [23]. Data on the saphenous trunks and varicose tributaries will be recorded in the study register. During the follow-up visits, patients in both study groups will be able to receive UGFS, if judged necessary by the patient, for the remaining or new tributaries. The additional treatments will be recorded in the study register.

A schematic diagram of the timeline of the study [31] is presented in Fig 1.

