## Statistical analysis

The sample size calculation for the study was based on the systematic review and meta-analysis by Aherne et al. [13]. Combined treatment of the saphenous trunk and varicose tributaries results in a 6.3% and staged treatment in a 36.1% reintervention rate. According to the power analysis, statistical dichotomous analyses between two independent groups with an alpha of 0.01, and a power of 80%, thus a 1:1 randomization would result in a sample size of 84. When calculated for a 12% difference, the anticipated sample size would, accordingly, be 228. Considering the long follow-up (5 years) and the anticipated large number of dropouts, the sample size was set at 260 (130 for each group).

For dropouts, the results will be analyzed until their last follow-up visit. If a patient has not completed their treatment or has not been treated according to their allocation (crossover), their participation in the study will be terminated and their data will not be included in the analysis.

All statistical analyses will be performed using SPSS version 27 for Mac (IBM, Armonk, NY, USA). Descriptive statistics will be used to summarize patient baseline characteristics. Mean values and standard deviations (SD) will be applied for continuous variables if normally distributed. Correspondingly, median values and interquartile range (IQR) will be applied for non-parametric variables. The Fisher’s exact test will be used to compare categorical variables, and the Wilcoxon Signed-Rank Test and the Mann-Whitney U test will be used to compare ordinal variables. Normally distributed continuous variables will be compared by using the Student’s t-test for values previously tested using the Shapiro–Wilk test. A *p*-value of < .05 will be considered statistically significant.

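### The stated 80% power does not hold under Fisher's exact test, the only test named for a binary outcome: about 74% at 84 patients, and 74% or 53% at 228 depending on alpha

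*Protocol article*

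**What the plan says.** All references are to the protocol article.

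- Outcome (Outcome measures and follow-up): "The primary outcome measure will be the need for additional treatment of the varicose tributaries during the follow-up, as judged by the patient". The sample size treats this as a comparison of two proportions.
- Test (Statistical analysis): Fisher's "exact test will be used to compare categorical variables". No separate test is named for the primary outcome.
- Rates (Statistical analysis): combined treatment "results in a 6.3% and staged treatment in a 36.1% reintervention rate".
- Sizing (Statistical analysis): 1:1 allocation "with an alpha of 0.01, and a power of 80" per cent gives 84 patients. Then: "When calculated for a 12% difference, the anticipated sample size would, accordingly, be 228". The total is set at 260, 130 per group, to allow for attrition over five years.
- Significance level for the analysis (Statistical analysis): a p-value "of < .05 will be considered statistically significant".
- Centres (Study design and data management; Patient enrolment and randomization): the trial is one "which will be conducted in four large Finnish hospitals". Allocation is through REDCap, and stratification by centre is neither stated nor excluded.

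**The concern.** A power statement holds for a particular test at a particular alpha. Here the sizes appear to come from one kind of calculation and the analysis uses another. With moderate group sizes and a low event rate in one arm, Fisher's exact test spends clearly less than its nominal alpha, so its power falls below what the approximate formula promises.

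The 12-point difference is the smaller of the two effects sized for, and its 228 patients underlie the 260. If the true difference is near 12 points, the margin from 228 to 260 is meant to absorb attrition. If the choice of test has already used up most of that margin, little is left for patients who drop out or who are removed because they were not treated as allocated.

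**Working it through.** **Inputs.** From the article: 6.3% and 36.1%; alpha 0.01 for sizing and 0.05 for analysis; 80% power; 84, 228 and 260 patients; 1:1 allocation. Assumed, because not stated: two-sided tests, and a 12-point difference read as 6.3% vs 18.3%.

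**Step 1: reproduce the sizes.**

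Pooled formula per group: n = [z(1−α/2)·√(2p̄(1−p̄)) + z(0.80)·√(p1(1−p1)+p2(1−p2))]² / (p1−p2)².

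For 36.1% vs 6.3% at alpha 0.01, p̄ = 0.212 and the two variances sum to 0.28971:

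n = (2.5758×0.5780 + 0.8416×0.5383)² / 0.298² = 3.771/0.0888 = 42.46.

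That is 86 in total when rounded up and 84 when rounded to the nearest whole patient per group.

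Unpooled formula per group: n = (z(1−α/2)+z(0.80))²·[p1(1−p1)+p2(1−p2)] / (p1−p2)².

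For 18.3% vs 6.3% the variances sum to 0.20854:

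- alpha 0.05: (1.9600+0.8416)²×0.20854/0.0144 = 113.7, so 114 per group and 228 in total. This is an exact match. The pooled formula gives 234.
- alpha 0.01: (2.5758+0.8416)²×0.20854/0.0144 = 169.1, so 340 in total. The pooled formula gives 348.

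For these rates, then, 228 reproduces at alpha 0.05 and not at 0.01.

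A continuity correction, which roughly mimics Fisher's test, does not reproduce the pair either. Two-sided, it gives 98 for the first comparison (alpha 0.01) and 266 (alpha 0.05) or 380 (alpha 0.01) for the second. One-sided at 0.01 it gives 86 and 332.

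**Step 2: power of the named test.** Exact enumeration: for every pair of event counts, apply the test and add up the binomial probabilities of the pairs that reject.

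| Rates | Total N | Alpha | Fisher | Pearson chi-square, uncorrected |
|---|---|---|---|---|
| 6.3% vs 36.1% | 84 | 0.01 | 74.4% | 81.7% |
| 6.3% vs 18.3% | 228 | 0.05 | 74.3% | 80.8% |
| 6.3% vs 18.3% | 228 | 0.01 | 52.9% | 59.8% |
| 6.3% vs 18.3% | 260 | 0.05 | 81.0% | 85.6% |
| 6.3% vs 18.3% | 260 | 0.01 | 59.0% | 65.3% |
| 6.3% vs 36.1% | 260 | 0.01 | >99.9% | >99.9% |

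Fisher's actual type I error at 114 per group and nominal 5% is 2.7%, 3.0% and 3.5% for common rates of 6.3%, 12% and 20%. Pearson's is 5.0% to 5.1%.

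**Step 3: patients needed under Fisher.** For 6.3% vs 18.3% at alpha 0.05, Fisher first reaches 80% at 128 per group, 256 in total (80.3%). The margin over 228 is 260−228 = 32. Fisher uses 256−228 = 28 of it and leaves 4. For 6.3% vs 36.1% at alpha 0.01 it needs 92 rather than 84.

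**Step 4: is centre the cause?** Simulation at 228 patients, alpha 0.05, 6.3% vs 18.3%, with four centres split 40/20/20/20, unstratified allocation and 6,000 runs per setting. CMH is the Cochran-Mantel-Haenszel test by centre; the centre SD is on the logit scale.

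| Centre SD | Fisher | Pearson | CMH, uncorrected | CMH, continuity-corrected | Exact stratified |
|---|---|---|---|---|---|
| 0 | 74.6% | 81.1% | 80.3% | 73.9% | 77.2% |
| 0.5 | 74.8% | 81.4% | 81.6% | 75.5% | 78.8% |
| 1.0 | 75.2% | 81.5% | 85.0% | 78.9% | 81.8% |

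Pearson also ignores centre, yet it recovers about 6.5 points. Going from Pearson to uncorrected CMH changes power by −0.8, +0.2 and +3.5 points.

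**The case against.** **Fisher's test is valid.** It controls the type I error, and being conservative is not an error. This stands. The point concerns the power figure attached to the test, not the validity of the result.

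**The trial enrols 260, not 84 or 228.** At the cited rates Fisher's power with 260 is above 99.9%, and for 6.3% vs 18.3% it is 81.0% at alpha 0.05. This also stands, and it limits the point. But 81.0% needs all 260 to be evaluable. The Statistical analysis section expects heavy attrition and removes patients who did not complete treatment or were not treated as allocated. Dropouts are kept to their last visit, so not all of the margin need be lost; the article does not say how much will be.

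**The base rate for the 12 points is assumed.** True. Read instead as 36.1% vs 24.1%, power at 228 and alpha 0.05 is 45% for Fisher and 51% for Pearson. Neither is near 80%, and the pooled formula would ask for 458 in total (229 per group). The article uses 228 as a total, since 260 is split into 130 per group.

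**A stronger reading: power is lost because four centres are ignored, and stratifying restores it at no cost.** The documents do not support this. Step 4 shows that nearly all of the gap is exact versus uncorrected large-sample testing. A continuity-corrected CMH recovers almost nothing at modest centre variation, and an exact stratified test gains about 2.5 to 4 points there. The article gives no centre sizes or centre variation. Centre adjustment is commonly left to an analysis plan, which is not shown, so its absence here is not a finding.

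**Conclusion.** The point holds as a mismatch between the stated power and the stated test. At 84 patients the shortfall is about 6 points on the article's own rates and alpha, assuming a two-sided test. At 228 patients, on the assumed 6.3% vs 18.3%, it is about 6 points at alpha 0.05 and about 27 at alpha 0.01. Most of the 27 arises because 228 does not follow from alpha 0.01: even Pearson reaches only 59.8% there, and Fisher's conservatism adds about 7 points.

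The practical consequence is confined to differences near 12 points, where almost all of the attrition margin is already spent. At 6.3% vs 36.1% with 260 patients nothing material is lost. A reader might infer that the trial is underpowered for its cited effect, or that the analysis is invalid; neither follows.

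**What to change.** Do one of the following before outcomes are compared between groups, and in either case state which alpha, 0.01 or 0.05, governs the primary comparison and which base rate the 12 points refer to.

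1. Keep Fisher's exact test as primary and restate its power for the number of patients expected to be evaluable.
2. Name an uncorrected large-sample test as primary: Pearson chi-square, or Cochran-Mantel-Haenszel by centre explicitly without continuity correction. Report a risk difference with a 95% confidence interval, keep Fisher's test as a sensitivity analysis and for sparse tables, and restate the power for the chosen test.

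Stratifying by centre is an optional refinement whose gain depends on how much centres differ. Either change costs wording and a short recalculation, with no extra patients or data. The small downside of the second is reliance on a large-sample approximation. In the simulations, uncorrected CMH kept its type I error at about 4.4% to 5.2% for a nominal 5%.

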**Methods:**

Consecutive patients with symptomatic varicose disease (CEAP clinical class C_2_–C_3_) will be screened for the study. Patients who fulfil the study criteria and give their informed consent will be scheduled for the procedure and randomized to either study group. Patients will be followed-up at 3 months, 1 year, 3 years, and 5 years. The post-procedure pain score based on a numeric rating scale (NRS) and also the use of analgesics, as well as possible procedure-related complications will be recorded at 3 months. Patient-reported outcome measures (PROMs) will be recorded at 1 year. Data pertaining to the additional treatment of varicose tributaries, the Aberdeen Varicose Vein Questionnaire (AVVQ), the Venous Clinical Severity Score (VCSS), and the health-related quality of life (EQ-5D-5L) will be collected at each follow-up visit. A duplex ultrasound (DUS) examination will be performed at each visit, and data on varicose tributaries and the need for additional treatment will be recorded.

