**Fig 1 pone.0285823.g001:**
[figure not shown]
Schedule of enrolment, interventions, and follow-up of the FinnTrunk study. The specific time points are listed in the columns and the events are given in the rows. Participants will be randomly allocated to EVLA without (x^1^) or with (x^2^) concomitant UGFS before procedure at the treatment visit. All participants will have a follow-up visit at 3 months, 1 year, 3 years, and 5 years. If found necessary, the varicose tributaries can be treated at any of the follow-up visits. Abbreviations: the Aberdeen Varicose Vein Questionnaire (AVVQ), (the clinical class of) the Clinical-Etiology-Anatomy-Pathophysiology classification (CEAP), endovenous laser ablation (EVLA), Duplex ultrasound (DUS), EuroQoL quality of life questionnaire (EQ-5D-5L), patient related outcome measures (PROMs), ultrasound-guided foam sclerotherapy (UGFS), the Venous Clinical Severity Score (VCSS), the Venous Disability Score (VDS). ^1^According to the randomized allocation (group 1) ^2^According to the randomized allocation (group 2) *If judged necessary by the patient (both groups).

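### The comparison of AVVQ, VCSS and EQ-5D-5L depends on a Shapiro–Wilk pretest, and no named between-group test adjusts for the recorded baseline score

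*Protocol article*

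**What the plan says.** Under Patient enrolment and randomization, patients complete the AVVQ and EQ-5D-5L and the investigator records the VCSS at enrolment, before treatment. The abstract lists the same three measures for repeat collection: "and the health-related quality of life (EQ-5D-5L) will be collected at each follow-up visit". The Fig 1 legend gives the schedule: "All participants will have a follow-up visit at 3 months, 1 year, 3 years, and 5 years". Each score thus has one baseline and four planned follow-up values.

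Table 1 asks whether the timing of tributary treatment matters for quality of life. Outcome measures and follow-up lists the effect of treatment on these scores among the other outcomes of interest, below the primary and secondary outcomes.

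The Statistical analysis section sets its rules by type of variable and does not name the three scores:

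- Continuous variables: "Normally distributed continuous variables will be compared by using the" "Student’s t-test for values previously tested using the Shapiro–Wilk test".
- Ordinal variables: "the Wilcoxon Signed-Rank Test and the Mann-Whitney U test will be used to compare ordinal variables".
- Summaries: mean and SD if normally distributed, otherwise median and IQR.

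The section names no test for a continuous variable that fails the normality check. It does not say which scores count as continuous or ordinal, or whether the tests are applied to final values or to changes from baseline.

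**The concern.** Two features of the stated rules work against the quality-of-life question.

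First, the quantity to be reported is not fixed in advance. For a score treated as continuous, a normality test on the trial data decides whether the t-test and the mean are used. The same score could yield a mean difference at 1 year and a rank comparison with medians at 3 years. Those results cannot be set on one scale, and a reader cannot follow the treatment effect over time.

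Second, the named between-group tests leave out information that the trial already collects. Neither the t-test nor Mann-Whitney takes a baseline covariate. Signed-rank is a paired test; used within an arm it describes change in that arm and does not compare the arms. The result is wider uncertainty than the data require, which matters most if the conclusion is that timing makes no difference. Chance imbalance in baseline scores is also not handled by adjustment.

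**Working it through.** **The plan's own figures.** The protocol gives no SD, correlation, target difference or power for these scores. Its sample-size figures concern reintervention. For 6.3% against 36.1% at two-sided alpha 0.01 and 80% power, the pooled formula gives 43 per arm, 86 in total, close to the stated 84, but this does not bear on the scores. Two arm sizes are taken from that section: 130 (the planned 260) and 114 (half of 228).

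**Assumptions not in the documents.** Baseline/follow-up correlation r between 0.3 and 0.7; equal variance at baseline and follow-up; and, for the power figures only, a true difference of 0.35 SD.

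**Step 1: precision.** Take the variance of the between-group difference relative to a comparison of final values:

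- final values: 1
- change scores: 2(1 − r)
- ANCOVA: 1 − r²
- ANCOVA relative to change scores: (1 − r²) / [2(1 − r)] = (1 + r)/2

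| r | Change score | ANCOVA | Reduction against final values | Reduction against change scores |
|---|---|---|---|---|
| 0.3 | 1.40 | 0.91 | 9% | 35% |
| 0.5 | 1.00 | 0.75 | 25% | 25% |
| 0.7 | 0.60 | 0.51 | 49% | 15% |

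At r = 0.7 the exact reduction against final values is 1 − 0.51 = 0.49; the 51% at the upper end of the range is the variance that remains, so the range of reductions is 9% to 49%. Change scores beat final values only when r exceeds 0.5. ANCOVA is better than both throughout this range.

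**Step 2: detectable difference.** At 130 per arm, two-sided 0.05 and 80% power, it is (1.960 + 0.842) × √(2v/130), with v the relative variance:

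- final values: 0.347 SD
- change scores: 0.411, 0.347 and 0.269 SD at r = 0.3, 0.5 and 0.7
- ANCOVA: 0.331, 0.301 and 0.248 SD

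**Step 3: power.** At 114 per arm and a 0.35 SD difference:

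- final values: 75%
- change scores: 61%, 75% and 93% at r = 0.3, 0.5 and 0.7
- ANCOVA: 79%, 86% and 96%

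**Step 4: how often the pretest switches the method.** Simulation with no group difference, 114 per arm and 4,000 replicates. Shapiro–Wilk is run in each arm at 0.05; the t-test is used if both arms pass and Mann-Whitney otherwise. That fallback is an assumption.

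| True distribution | Rank test chosen | Type I error of the two-stage rule |
|---|---|---|
| Normal | 10% | 5.0% |
| Skewness 0.25 | 28% | 5.3% |
| Skewness 0.5 | 71% | 5.3% |
| Skewness 1 | about 100% | 5.0% |
| Integer score, SD 2.5 | 86% | 5.4% |

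**Step 5: mixed methods for one score.** If the rank test is chosen with probability p at each of four visits, treated as independent, the chance of mixed methods is 1 − p⁴ − (1 − p)⁴. This is 34% for p = 0.1 or 0.9, and 75% for p = 0.3 or 0.7. Positive dependence between visits would lower these figures.

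**The case against.** The strongest reply is that much here is silence, and that a journal article may leave modelling detail to a full analysis plan. Several stronger readings are tempting, and the documents do not support them:

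- **That the baseline is discarded.** The section does not exclude t-tests or Mann-Whitney on change from baseline, and it lists the paired signed-rank test. What stands is that no named between-group test adjusts for baseline; Step 1 shows a loss on either reading.
- **That Mann-Whitney is the written fallback after a failed normality test.** It is assigned to ordinal variables. Using it as the fallback is a natural reading, but only a reading.
- **That all three scores are subject to the pretest.** If VCSS, say, is handled as ordinal, no pretest applies to it. The instability then disappears for that score, though the missing baseline adjustment remains.
- **That centre is ignored, or that a patient who misses a visit is lost from that visit's test.** The section states neither.
- **That the tests are invalid.** Unadjusted tests are valid in a randomized trial, and the simulated type I error stayed between 5.0% and 5.4%.

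It is also fair that the size of the gain rests on an assumed correlation. At r = 0.3 the detectable difference moves only from 0.347 to 0.331 SD against final values.

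The point survives because the article does not defer the choice: it names the tests and makes one of them depend on the observed data.

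**Conclusion.** The point holds in this limited form. For any score treated as continuous, the stated rule lets the data decide the test and the summary, so the reported quantity is not fixed beforehand and may differ between visits. For all three scores, the named between-group tests do not adjust for a baseline that is on record.

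The cost is interpretability and precision, not false positives. By the formula 1 − r², the variance reduction from ANCOVA is 9% at r = 0.3, 25% at r = 0.5 and 49% at r = 0.7 against final values (leaving 51% of the variance in the last case); against change scores it is 35%, 25% and 15%. These figures rest on the assumed correlations and, for change scores, on equal variances. The switching frequencies rest on the assumed distributions, the assumed Mann-Whitney fallback and independent visits.

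Severity is low to moderate: the scores are other outcomes of interest, and the primary outcome is untouched.

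**What to change.** For each of AVVQ, VCSS and EQ-5D-5L, prespecify one effect measure: the baseline-adjusted mean difference between groups with its 95% CI at each follow-up visit. Estimate it either by ANCOVA at each visit or by one linear mixed model per score with group, visit, their interaction and the baseline score. Use robust or bootstrap standard errors to allow for skewness.

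Drop the Shapiro–Wilk switch for these scores, and keep Mann-Whitney as a sensitivity analysis that is reported whatever the distribution looks like. If a full analysis plan already specifies such a model, align the published section with it.

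The cost is a change of analysis wording and slightly more analysis work. All the data are already scheduled for collection, and neither the sample size nor the visits change.
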